### Schedule of assessments

Patients will attend for a total of 14 visits over a period of just over 12 months (Fig. 1). Evaluation of CMV reactivation by deoxyribonucleic acid (DNA) PCR of blood and urine will be done monthly. Evaluation of the tolerability of the drug and adverse events will occur monthly. Immune assessments as detailed below and in Table 1 will be performed at entry, 6 months and 12 months (Fig. 1).

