### Sample size calculation and planned statistical analyses

In an immunocompetent elderly population, CMV reactivation occurred in 90 % at 6 months [18]. It is expected that CMV reactivation will be at least that in our immunosuppressed population. Information for dosing regimens using antiviral prophylaxis in renal transplant recipients has demonstrated over 90 % suppression of CMV reactivation. Our sample size assumes 90 % reactivation in the control limb and a conservative estimate of 50 % reactivation in the treated group. The estimated sample size is 50 patients, 25 patients in each arm, based on 80 % power at a significance level of *p* < 0.05 (two-tailed test).

All analyses will be performed using the intention-to-treat principle. Baseline covariates will be compared between the two arms to observe the balance and the success of randomisation. The primary analysis will test the hypothesis that there is no difference in the proportion of patients with CMV reactivation between those receiving antiviral prophylaxis compared with those receiving usual treatment. For the secondary outcomes, comparisons will be made between groups using absolute measures of immune function and change between data at entry and end of treatment within groups. Missing data will be dealt with by simple imputation if missing randomly. Where data are missing systematically, appropriate statistical models will be applied to avoid attrition bias. A full statistical analysis plan will be written and approved prior to data analysis.

A safety analysis will be performed on all treated patients. The number of events and incidence of adverse events by system organ class will be summarised and the relationship to the treatment noted.

The final report will follow the CONSORT 2010 guidelines and will be published in a peer-reviewed journal. Authorship will be based on the International Committee of Medical Journal Editors guidelines. Results will be communicated to study participants and patient groups through presentations at patient and carer group meetings.

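### The protocol fixes single fill-in of values for randomly missing data, where none is needed; depending on the form, this understates uncertainty or shrinks the treatment effect

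*Protocol article*

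**What the plan says.** The section Sample size calculation and planned statistical analyses has two rules for missing data. The first is "Missing data will be dealt with by simple imputation if missing randomly". The second is "Where data are missing systematically, appropriate statistical models will be applied to avoid attrition bias". The same section says that a full statistical analysis plan will follow and that analyses are by intention to treat.

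The article does not say which simple imputation is meant, whether it applies to visits or to patients, or whether it covers the primary outcome. It gives no expected missing fraction.

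The primary outcome is a per-patient proportion with CMV reactivation. On sampling, the section Schedule of assessments says "Evaluation of CMV reactivation by deoxyribonucleic acid (DNA) PCR of blood and urine will be done monthly". Table 1 defines the main secondary outcomes as changes from baseline to 6 months.

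**The concern.** The natural reading of simple imputation is that one value is filled in for each gap and then analysed as if it had been measured. That adds no information, yet the analysis counts the filled value as a full observation. The choice also falls on the one case, random missingness, in which the observed values already support a valid comparison.

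What is at stake is the trustworthiness of the secondary results: the proportion of CD4+CD28null cells and the inflammatory markers. The Discussion section wants these findings to enable larger studies, so effect estimates and their intervals matter as much as p-values.

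The choice between the two rules also depends on deciding whether data are missing randomly. Observed data cannot establish that in general, and with 25 per arm a few patients could decide it.

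**Working it through.** **Arm size.** The article states "Our sample size assumes 90 % reactivation in the control limb" and "a conservative estimate of 50 % reactivation in the treated group", with 80% power and two-sided 5% significance.

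- Uncorrected: n = [1.96·√(2·0.7·0.3) + 0.8416·√(0.9·0.1 + 0.5·0.5)]² / 0.4² = (1.270 + 0.491)² / 0.16 = 19.4, so 20 per arm.
- With continuity correction: (19.4/4)·[1 + √(1 + 4/(19.4·0.4))]² ≈ 24.1, so 25 per arm.

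This reproduces "The estimated sample size is 50 patients, 25 patients in each arm". The checks below use 25 per arm.

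**Assumptions.** Missing fraction m of 10% or 20%; continuous change score; missing completely at random, equally in both arms; two-sample t-test at 5%.

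**Arm-mean fill, closed form.** The filled values have no spread, so the estimated variance is about (1−m)σ² and is divided by n instead of n(1−m).

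- Standard error used: √[2(1−m)σ²/n].
- True standard error: √[2σ²/(n(1−m))].
- The test statistic is therefore too large by a factor 1/(1−m), and the actual type I error is 2·[1 − Φ(1.96·(1−m))].
- m = 0.10: 2·[1 − Φ(1.764)] = 7.8%.
- m = 0.20: 2·[1 − Φ(1.568)] = 11.7%.

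**Pooled-mean or zero-change fill, closed form.** Both arms receive the same constant c, so each filled arm mean is (1−m)·(observed mean) + m·c. The difference becomes (1−m) times the observed difference. A true 0.8 SD at m = 0.20 becomes 0.8 × 0.8 = 0.64 SD.

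**Simulation** (20,000 trials per setting under no effect; 40,000 with a true difference of 0.8 SD):

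| Method | Type I error, 10% / 20% missing | Estimate of 0.8 SD at 20% missing | Coverage of 95% interval at 20% missing |
|---|---|---|---|
| Observed values only | 5.1% / 5.0% | 0.80 | 95% |
| Arm-mean fill | 8.1% / 11.9% | 0.80 | 88% |
| Pooled-mean fill | 5.1% / 5.0% | 0.64 | about 90% |
| Zero-change fill | 5.1% / 5.0% | 0.64 | about 90% |

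A random draw from observed values in the same arm (hot deck) gives a type I error of 7.7% / 10.4%.

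**Primary outcome.** Take a 90% rate in both arms, 20% of patients missing and a random within-arm fill. Type I error is then 9.8% by chi-square but 2.9% by Fisher's test. Filling with the arm's most frequent value gives 4.1% by chi-square. Any inflation here therefore depends on the form of fill and on the test, and the article names neither.

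**The case against.** The strongest reply is that the article is a condensed account, promises a full analysis plan, and does not say which imputation it means. Some forms keep the error rate at 5%, so it is not true in general that the plan inflates type I error. That stands, and the claim of inflation is limited to within-arm forms. It does not rescue the rule. Every mean or zero-change fill tested loses coverage once there is an effect to estimate, while using observed values loses nothing. An analysis plan that followed the sentence would inherit the problem.

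A reader might go further and infer that the plan counts a patient not tested as a patient without reactivation, so that early leavers on valaciclovir would make an inactive drug look effective. As an illustration, suppose any positive result over six independent monthly tests counts as reactivation. A 90% rate then implies 1 − 0.1^(1/6) = 31.9% per test, and a patient tested only twice is found positive 1 − 0.681² = 54% of the time. If 20% of the valaciclovir arm left after month 2 and were scored on those two tests, the arms would read 0.8·90% + 0.2·54% = 83% against 90%.

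The documents do not support presenting this as a result of the plan:

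- No sentence scores an untested visit or patient as negative, and imputing a value is a different operation.
- The any-positive definition up to month 6 is inferred, not stated.
- Independence of monthly tests is assumed. If patients differ in their underlying rate, 54% is the lowest value; with an intra-patient correlation of 0.1 to 0.3 it becomes 61% to 72%.
- The example needs unequal dropout, which the protocol assigns to its second rule. With equal missingness, and untested visits counted as negative, type I error is 5.2% to 5.7% by chi-square.
- Patients who stop the drug are asked whether they will keep attending, so stopping treatment need not mean missing tests.

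What remains is a risk to guard against. Only one arm takes a drug in this open-label trial, so unequal dropout is plausible. If it occurred in the valaciclovir arm only, at 20% by month 6, and untested visits were counted as negative, type I error would be 12.7% by chi-square and 5.2% by Fisher's test.

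**Conclusion.** The point holds for the stated commitment to simple imputation under random missingness, chiefly for the continuous secondary outcomes. At 10% to 20% missing, arm-mean fill takes a nominal 5% error to about 8% to 12%. Pooled-mean or zero-change fill at 20% missing costs one fifth of the effect and about five points of coverage. Observed-data analysis avoids both.

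These sizes rest on assumed missing fractions, on data missing completely at random and equally in both arms, and on my reading of simple imputation as a single filled value. For the primary outcome no definite bias can be attributed to the plan; the handling of missed PCR tests simply should not rest on this sentence. The change is worth making because it is cheap and the present wording points the analysis plan to an inferior method.

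**What to change.** Delete the commitment to simple imputation. For the secondary outcomes, analyse the observed data with a likelihood-based model that adjusts for the baseline value, or use multiple imputation.

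For the primary outcome, first state whether reactivation means any positive monthly PCR up to month 6. If it does, handle missed visits by multiple imputation at visit level, or estimate cumulative reactivation at month 6 with a discrete-time model of the first positive visit. Add a sensitivity analysis adverse to valaciclovir, scoring missing results as positive on valaciclovir and negative on control.

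The cost is a change of wording in the protocol and the analysis plan and a few hours of programming. Confidence intervals will be slightly wider than after arm-mean fill, which is the honest width.

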### Participants

In total, 50 CMV seropositive patients with AAV in stable remission for 6 months or longer and on a maximum of two immunosuppressant agents will be recruited from the Vasculitis Clinic at UHB NHS Foundation Trust. Recruitment will take place over 2 years. Our tertiary referral vasculitis clinic has more than 200 patients under long-term follow-up. Approximately 90 % of patients are in remission at any one time and 70 % are seropositive for CMV. CMV status is checked routinely at the patient’s first attendance in the clinic. We anticipate that 125 of our patients attending the clinic will be eligible for this study. Recruitment of 40 % would achieve the target of 50 patients. This is a conservative rate given our previous experience. Patients will be approached at routine clinic visits. Patients may also be contacted via post by sending them a copy of the patient information sheet (see Additional file 2). Patients will be allowed a minimum of 24 hours to reflect on the content of the patient information sheet before written informed consent is obtained by completion and signing of the study-specific informed consent form (see Additional file 3).

A full list of study inclusion and exclusion criteria is given in Table 2. Subjects will be withdrawn from the trial if they choose not to continue or the investigators feel that continued participation in the trial is inappropriate. Subjects who withdraw from the intervention will be asked if they are prepared to continue to attend follow-up clinics. The study’s primary and main secondary outcomes are based on objective laboratory assays, therefore, minimising the risk of performance bias in this open-label design. Furthermore, treatment and medical management other than valaciclovir will be identical between the treated and control patients.

**Table 2 Tab2:** Study inclusion and exclusion criteria

Inclusion criteria	
	Documented diagnosis of granulomatosis with polyangiitis (Wegener’s), microscopic polyangiitis or renal limited vasculitis according to Chapel Hill Consensus Conference Criteria
	In stable remission (no documented clinical disease activity) for at least 6 months prior to study entry
	On maintenance immunosuppression with prednisolone, mycophenolate mofetil or azathioprine alone or in combination (maximum two agents)
	Documented past evidence (any time point) of CMV infection (CMV-specific immunoglobulin G detected in peripheral blood)

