**Fig. 1 Fig1:**
[figure not shown]
SPIRIT figure showing study’s schedule of enrolment, intervention and assessment. *M0* baseline visit, *M1* to *M12* month 1 to month 12, *qPCR* quantitative polymerase chain reaction. *Safety blood tests will be performed only on treatment group

After providing written informed consent, the patients will undergo an initial pre-baseline visit. During this visit, a 5-ml blood sample will be drawn, which will be used to determine the percentage of CD4 + CD28null cells. This value will be utilised in the randomisation of patients as explained below.

At the baseline, 6-month and 12-month visits, a total of 50 ml of blood will be drawn in addition to a 50-ml sample of urine. The samples will be used to determine CMV viral copies by DNA PCR in blood and urine (primary outcome), the proportion of CD4 + CD28null cells in peripheral blood by flow cytometry (secondary outcome), the concentration of soluble markers of inflammation (Table 1) in peripheral blood (secondary outcome) and immune assessments and T-cell phenotyping as detailed in the exploratory outcomes (Table 1). Excess sample will be stored appropriately. Blood pressure and arterial stiffness measurements will also be carried out at the baseline, 6-month and 12-month visits as detailed below.

During the remainder of the monthly visits, a 10-ml blood sample will be drawn in addition to a 50-ml sample of urine, which will be used to determine CMV viral copies by DNA PCR in blood and urine (primary outcome). Excess sample will again be stored appropriately. In addition, safety blood tests as defined below will be performed monthly for the duration of treatment for those patients randomised to receive the drug.

Appointments will be scheduled on monthly with an allowance of 10 days either side of the estimated due date of the monthly appointment to allow for patient convenience and flexibility. The overall treatment period (or control period) of 6 months will also be subject to the same 10-day rule to avoid excessive movement of the length of treatment.

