### Treatment

Patients randomised to the treatment arm will receive 2 g of valaciclovir orally four times a day. The dose will be reduced appropriately depending on renal function (Table 3). The study is open label and valaciclovir will be used off the shelf with no modifications to the packaging or labelling of the product. Patients will be asked to return unused tablets at each monthly visit to monitor compliance with medication. Patients randomised to the control arm will receive no additional treatment. Safety blood tests will be conducted monthly for the duration of treatment for the patients randomised to valaciclovir and these will comprise a full blood count, urea and electrolyte levels, and liver function tests. In the event of toxicity of grade 2 or less (scored using the National Cancer Institute (NCI) Common Terminology Criteria for Adverse Events version 4.0), the adverse event will be discussed with one of the investigators to determine whether drug administration should be temporarily withdrawn or the dose reduced. In the event of toxicity of grade 3 or more, the adverse event will be discussed with the principal investigator. In such a case, the expectation will be to withdraw drug administration for 1 week unless the adverse event is judged by the principal investigator to be unrelated to the study drug. Reintroduction of the drug will be based on a clinical review. The collection and reporting of data on adverse events and serious adverse events will be in accordance with EU directive 2001/20/EC and UK legislation.

**Table 3 Tab3:** Dose modification of valaciclovir according to creatinine clearance

Creatinine clearance (CrCl ml/min)^a^	Valaciclovir dose
>75	2 g four times a day
51–75	1.5 g four times a day
26–50	1.5 g three times a day
10–25	1.5 g two times a day

^a^Tests performed within 6 months of the pre-baseline visit can be used for this assessment

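### Adverse event counts and incidence, a secondary safety measure, are to be summarised in the valaciclovir arm alone, without the randomised controls

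*Protocol article*

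**What the plan says.** All references are to the protocol article.

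- **Status of safety.** Methods/design and Table 1 make safety a secondary outcome. Table 1 gives it two measures: adverse event counts with incidence by system organ class, and adverse events serious enough to end study drug.
- **Analysis set.** Under Sample size calculation and planned statistical analyses: "A safety analysis will be performed on all treated patients". The content follows: "The number of events and incidence of adverse events by system organ class will be summarised and the relationship to the treatment noted".
- **Between-group comparison.** The same section plans comparisons between groups for the secondary outcomes, but words them for measures of immune function. Safety is not named there.
- **Event collection.** Under Schedule of assessments: "Evaluation of the tolerability of the drug and adverse events will occur monthly". No arm is singled out.
- **Laboratory safety.** The Fig. 1 legend says "Safety blood tests will be performed only on treatment group". The Treatment section agrees: blood count, urea and electrolytes, and liver function are tested monthly in patients randomised to valaciclovir, while they are on treatment.
- **Controls.** Under Treatment: "Patients randomised to the control arm will receive no additional treatment". There is no placebo.

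**The concern.** The first Table 1 measure applies equally to both arms, and the monthly visits appear to collect the data for it in both. Limiting its analysis to the valaciclovir arm gives up the one feature of the design that separates drug effect from background.

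Background matters here. Participants have ANCA-associated vasculitis and take prednisolone, mycophenolate mofetil or azathioprine, up to two agents. Only stage 5 chronic kidney disease is excluded, and Table 3 provides for creatinine clearance down to 10 ml/min. Infections and abnormal blood results are to be expected without valaciclovir, although the article gives no rate for them.

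The plan offers a judgement of each event's relationship to treatment instead. In an open-label trial that judgement is made knowing the allocation, and it does not replace a concurrent comparator. The Discussion says the results should enable larger studies, so the safety figures are likely to be used.

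**Working it through.** **Step 1: who the treated patients are.** The phrase could be a stock label for everyone who received assigned treatment. The article's own usage points elsewhere.

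- Participants section: "treatment and medical management other than valaciclovir will be identical between the treated and control patients". Treated and control are opposites.
- Sample size section, where the safety sentence also stands: "Our sample size assumes 90 % reactivation in the control limb and a conservative estimate of 50 % reactivation in the treated group". The contrast is the same.
- Controls receive nothing and there is no placebo, so a control patient cannot be treated in the sense of having received study medication.

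The plain reading is the valaciclovir arm.

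**Step 2: which measures this affects.**

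| Table 1 safety measure | Can occur in controls? | Is a valaciclovir-only set right? |
|---|---|---|
| Event counts and incidence by system organ class | Yes | No, the comparator is left out |
| Events sufficient to stop study drug | No | Yes |

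**Step 3: arm size.** The plan states no figure for safety, so there is none to reproduce. The illustration needs 25 per arm, and that figure does reproduce from 90% versus 50% reactivation, 80% power and two-sided 0.05:

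- Uncorrected: n = [1.96·√(2·0.7·0.3) + 0.8416·√(0.9·0.1 + 0.5·0.5)]² / 0.4² = (1.270 + 0.491)² / 0.16 = 19.4, so 20 per arm.
- Continuity-corrected: (19.4/4)·[1 + √(1 + 4/(19.4·0.4))]² = 24.1, so 25 per arm and 50 in total, as stated.

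**Step 4: what a one-arm rate can show.** The event counts here are assumed, because the article gives none. Suppose 10 of 25 valaciclovir patients have at least one event. The treated-only analysis reports 40% (exact 95% CI 21% to 61%), whatever happens in controls. With the control arm, risk difference = p_T − p_C, and the Wald 95% CI is ± 1.96·√[p_T(1−p_T)/25 + p_C(1−p_C)/25]:

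| Controls with an event | Risk difference (points) | 95% CI |
|---|---|---|
| 0 of 25 (0%) | +40 | 21 to 59 |
| 5 of 25 (20%) | +20 | −5 to 45 |
| 10 of 25 (40%) | 0 | −27 to 27 |

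For the middle row: √(0.24/25 + 0.16/25) = 0.1265, and 1.96 × 0.1265 = 0.248. The first row's interval is too narrow, because the Wald formula gives a zero count no variance. The exact upper limit for 0 of 25 is 13.7%.

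A rarer event behaves the same way. Five of 25 treated patients is 20% (exact 95% CI 7% to 41%), which means one thing against 0 of 25 controls and another against 5 of 25.

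**Step 5: laboratory ascertainment.** The protocol requires up to 25 × 6 = 150 safety panels in the valaciclovir arm and none in controls. A by-arm table that pooled all events would include some that only one arm was systematically tested for, which would count against valaciclovir. These events have to be kept apart.

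**The case against.** The strongest reply is that the main text defines safety as events sufficient to stop valaciclovir, which controls cannot have, so a drug-arm set is natural. That is right for this measure. It does not cover the other Table 1 measure, which the safety paragraph itself says will be summarised.

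A second reply is that control events are probably collected and that the full analysis plan, not shown, may tabulate them. A reader might infer that control event data are lost, and the article does not support that. But it states the analysis set outright, so this is a stated choice and not a detail left open.

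A third reply is that 25 per arm is too few for a safety comparison. It is too few for a powered one. A descriptive comparison with honest intervals still tells more than a single-arm rate.

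Three stronger readings are tempting and should not be drawn:

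- **That one-arm blood tests contradict the promise of identical management.** That sentence excepts valaciclovir. The tests are described under Treatment, for the duration of treatment, beside the rules for pausing or reducing the drug, so they can fairly be read as part of giving it.
- **That the monthly results could change immunosuppression in one arm and so bias the primary outcome.** Nothing in the article says results are used that way. The only responses described concern the study drug, and CMV PCR is monthly in all patients.
- **That the same tests could simply be run on control blood already drawn.** The 10 ml monthly sample is for CMV PCR. Nothing shows that it would suffice, and this would change trial conduct, not analysis.

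The general statement "All analyses will be performed using the intention-to-treat principle" also sits awkwardly with a treated-only set. Separate safety sets are common, however, and the point does not depend on it.

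**Conclusion.** The concern holds for one measure: adverse event counts and incidence by system organ class. As written, this would be reported for about half of the randomised patients, without its comparator, and could not be attributed to the drug or to background. In the illustration, one observed rate of 40% fits an excess anywhere from 0 to 40 points.

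This rests on reading treated as the valaciclovir arm, which the article's usage supports, and on adverse events being recorded in controls at the monthly visits, which the schedule implies but does not spell out. The event counts are assumptions.

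A reader might infer that the whole safety outcome is uninterpretable. It is not: events sufficient to stop study drug are rightly reported in one arm. The primary analysis is unaffected.

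**What to change.** Replace the sentence that defines the safety set with wording to this effect:

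- Adverse events are summarised by arm for all randomised patients, as patients with at least one event and as event counts, overall and by system organ class. The proportions are given with a risk difference and 95% CI. The comparison is descriptive.
- Events found only through the protocol safety blood tests are listed separately for the valaciclovir arm and not compared between arms.
- Events sufficient to stop study drug are reported for the valaciclovir arm only.

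The change is to analysis wording and table layout. It needs no new visits, samples or tests, but each event must carry a flag for whether it was found only through the safety bloods. The cost is slightly more tabulation and wide intervals, with half-widths of roughly 19 to 27 points in the illustration, which the report should state plainly.
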